##### Other outcomes

3.2.4.3

Compliance: Slimming World records include attendance, quantity of sessions and weight at first and last sessions (intervention group only).Blood Pressure: Blood pressure (automated, average of last 2 of 3 measurements taken in non-dominant arm after being seated for 5 minutes).Follow up analysis of those women who have a further pregnancy within 12 months to document: BMI at booking, development of GDM and birth weight.Partner weekly step count (if applicable)

#### Data collection and management

3.2.5

All instruments will be administered to participants by the researchers and all data, including that obtained from patient notes to record usual care/treatment, will be collated on a study-specific case report form starting at the time of recruitment. Data will be maintained and managed by the PAIGE2 research team within the Belfast Health and Social Care Trust (sponsor). OGTTs and fasting blood samples will be analyzed and stored within the Regional Centre for Endocrinology and Diabetes, Royal Victoria Hospital, Belfast. Trial recruitment will be monitored by the Principal Investigator and a project manager will coordinate all aspects of the trial and manage and analyze all data under their supervision. An educational clinical psychologist will provide advice on the psychological aspects of the study including motivational interviewing and a statistician will oversee randomization and data analysis. All paper and electronic records relating to the study will be retained for 5 years.

### Data analysis

3.3

#### Statistical analysis

3.3.1

Primary and secondary outcomes at 12 months will be compared between the intervention and control groups using analysis of covariance to adjust for any differences at baseline and so produce an estimate of the intervention effect with 95% confidence limits. Adjustment will also be made for recruitment center and any characteristics relevant to the outcome which, by chance, show imbalance between groups. Prior to analysis, logarithmic transformations will be applied to those secondary outcome variables whose distributions show marked positive skew. A correction will be applied to standard errors of intervention effect estimates to make allowance for the clustered nature (by week) of the randomization, although analysis of the pilot study (which used the same randomization procedure) indicated that this will make little difference to the findings. To help assess the impact of non-response, sensitivity analyses will be conducted on key outcomes by multiple imputation of missing values by chained estimating equations using the commands provided in the Stata package (StataCorp, College Station, TX). We will use this approach to impute 10 complete datasets and analyze them appropriately to provide results which take account of missingness. For key outcome variables, this analysis will be reported in addition to the complete case analysis. Analysis will be by intention to treat.

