#### Study setting

3.1.2

A six center, two parallel arm, randomized controlled trial, with an equal allocation ratio of intervention to control group participants will be conducted. The six centers will include antenatal-metabolic clinics at the Royal Jubilee Maternity Service, Belfast; Ulster Hospital, Dundonald; Antrim Area Hospital; Our Lady of Lourdes Hospital, Drogheda; Sligo University Hospital and Letterkenny University Hospital.

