#### Randomization

3.1.4

To streamline the organization of the intervention, economize on staff time and avoid contamination effects, women will be randomized to treatment group according to the week they attend for review at the joint diabetes antenatal clinic at 32-26 week’s gestation. Delivery of the intervention or control program will take place weekly at each site in person or *via* telephone or video call. Weeks will be allocated at random, using a restricted randomization developed earlier. To minimize the risk of manipulation, allocations will only be made available to recruitment centers on the morning of the visit in sufficient time for necessary administrative arrangements to be made. Women who agree to participate at 32–36-week gestation but who did not subsequently turn up for their postnatal follow-ups must be considered as having been recruited but lost to follow-up. Due to the nature of the intervention, the study cannot be blinded. The number of women randomized to each schedule will be reviewed regularly by the trial statistician to ensure that approximately equal numbers are assigned to treatment group. Should a serious imbalance develop, an additional intervention or control week will be added as appropriate.

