#### Sample size

3.1.7

Assuming the same variability in weight loss as was observed in the pilot study (52) (standard deviations of 7.0 and 3.9 kg in the intervention and control groups, respectively) and a 40% drop out rate (including women diagnosed with overt diabetes on the basis of a fasting glucose sample postnatal), it is estimated that a trial of 340 women should yield 200 evaluable subjects (100 in each of the intervention and control groups) which will be sufficient to detect a 3kg difference in maternal weight at 12 months after delivery with >90% power at the 5% level of significance.

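### Extra covariates enter the model only if they happen to be imbalanced, so the model depends on the draw; a short prognostic list fixed in advance would be better

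*Protocol article*

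**What the plan says.** Section 3.3.1 (Statistical analysis) compares primary and secondary outcomes at 12 months "using analysis of covariance to adjust for any differences at baseline and so produce an estimate of the intervention effect with 95% confidence limits". Section 3.2.4.1 confirms that for the primary endpoint this means 12-month weight allowing for baseline weight. The model is then extended: "Adjustment will also be made for recruitment center and any characteristics relevant to the outcome which, by chance, show imbalance between groups".

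So two terms, the baseline value and centre, are fixed. Any further term must pass two tests: it must be relevant to the outcome, and it must turn out to differ between the arms. The rule covers primary and secondary outcomes alike. Section 3.1.4 adds: "Due to the nature of the intervention, the study cannot be blinded".

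**The concern.** Under random allocation, chance differences between arms are already allowed for in the standard error. A covariate earns its place by how well it predicts the outcome, and that can be judged before any data are seen. Making entry conditional on observed imbalance has three consequences.

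- **The model varies with the draw.** Two trials run identically would be analysed with different covariates.
- **The reported standard error does not match the procedure.** Large chance imbalances are removed when they occur, so the estimate varies less than the reported standard error implies.
- **Precision is forgone.** A strong predictor that looks balanced is left out, and its variance stays in the residual.

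There is also an opening for choice. With no list fixed in advance in an open-label trial, what counts as relevant or imbalanced could be settled late.

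This is a rule that the article states, not detail left to an analysis plan. A plan that followed the sentence would inherit the problem, and one that fixed its covariates would contradict the sentence.

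**Working it through.** **Inputs from section 3.1.7.** "standard deviations of 7.0 and 3.9 kg in the intervention and control groups, respectively"; "a 40% drop out rate"; 100 evaluable women per arm; a design "sufficient to detect a 3kg difference in maternal weight at 12 months after delivery with >90% power at the 5% level of significance". Section 3.1.2 gives 1:1 allocation. Two-sided testing is assumed, in line with the 95% limits.

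**Assumptions, because the article gives no figures.** Five independent candidate covariates; together they explain R² = 10%, 30% or 50% of outcome variance; imbalance is declared at p<0.05 or p<0.20. Women are treated as individually randomised, so clustering by clinic week is not modelled.

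**Step 1: the plan's own figure.**
- Pooled SD = √[(7.0² + 3.9²)/2] = 5.67 kg.
- SE = 5.67 × √(2/100) = 0.80 kg.
- Power at 3 kg = Φ(3/0.801 − 1.96) = Φ(1.78) = 96.3%, or 96.1% with a t test. The stated figure of more than 90% is reproduced.
- 200/0.6 = 334 against 340 stated, and 340 × 0.6 = 204 evaluable. This agrees.

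**Step 2: how often the model changes.** The chance that at least one of five candidates looks imbalanced is 1 − 0.95⁵ = 23% at p<0.05 and 1 − 0.80⁵ = 67% at p<0.20. The simulation gave about 22% and 67%.

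**Step 3: the rule applied mechanically, no true effect (6,000 runs per row).**

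| R² | Threshold | Mean reported SE | True SD of estimate | Ratio | Type I error |
|---|---|---|---|---|---|
| 10% | 0.05 | 0.801 | 0.789 | 1.015 | 4.9% |
| 10% | 0.20 | 0.799 | 0.779 | 1.026 | 4.5% |
| 30% | 0.05 | 0.797 | 0.770 | 1.035 | 4.4% |
| 30% | 0.20 | 0.781 | 0.732 | 1.067 | 3.9% |
| 50% | 0.05 | 0.792 | 0.750 | 1.056 | 4.3% |
| 50% | 0.20 | 0.763 | 0.671 | 1.137 | 2.4% |

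Simulation error is about 1/√(2 × 6,000) = 0.9% on each SD and √(0.05 × 0.95/6,000) = 0.3 points on each type I error. The first row is therefore hardly distinguishable from nominal.

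A large-sample formula gives the same pattern. With threshold α, critical value c and q = (1 − α) − 2cφ(c), the ratio is √[(1 − αR²)/(1 − R² + qR²)]. Here q = 0.721 at α = 0.05 and 0.350 at α = 0.20.
- R² 10%: √(0.995/0.972) = 1.012 and √(0.980/0.935) = 1.024.
- R² 30%: √(0.985/0.916) = 1.037 and √(0.940/0.805) = 1.081.

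Adjusting for all five covariates by plan, mean SE and true SD agree (0.769 and 0.768; 0.678 and 0.676; 0.573 and 0.569 for the three values of R²), and type I error is 4.8% to 5.4%.

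**Step 4: power, imbalance rule at p<0.05 against the fixed list (3,000 runs each).**

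| R² | 3 kg: rule | 3 kg: fixed | 2 kg: rule | 2 kg: fixed |
|---|---|---|---|---|
| 10% | 96.6% | 97.3% | 69.8% | 73.3% |
| 30% | 96.4% | 99.2% | 70.7% | 83.2% |
| 50% | 97.2% | 100% | 72.6% | 93.8% |

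For R² of 10% to 30% the loss is 0.7 to 2.8 points at 3 kg and 3.5 to 12.5 points at 2 kg.

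**The case against.** The strongest defence is that little of the model is open. Baseline weight, probably the best single predictor, and centre are fixed, so what the remaining covariates can add is limited and the R² 10% rows are the more realistic. The sentence also requires relevance to the outcome, so it is not a pure imbalance rule. Applied as written it errs on the safe side, and the trial still exceeds its stated power at 3 kg. All of this stands and keeps the point modest.

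It can also be said that imbalance here need not be pure chance: weeks rather than women are allocated, and 40% dropout is expected. That is fair, and it means the simulation, which ignores clustering, is only indicative. It does not support selecting on imbalance: a difference between arms caused by differential loss is not a chance imbalance, and it calls for a missing-data analysis.

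A reader might infer that the rule inflates false positives. If the analyst took the smallest p-value among three models (unadjusted, imbalance-adjusted, fully adjusted), type I error would rise to 6.7% to 8.8%. The documents do not support that charge. Selection is on baseline comparisons, which need no outcome data, and nothing says results will be in view. Nor does the article say that the analyst is unblinded when covariates are chosen: section 3.1.4 ties the lack of blinding to the nature of the intervention, and section 3.2.5 says only who analyses and oversees the data. What stands is that the text does not close this route.

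The missing threshold and candidate list could properly sit in an analysis plan that is not shown. The objection here is to the stated principle of selection, not to those omissions.

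**Conclusion.** The point holds in a limited form. The baseline value and centre are fixed, but further covariates enter because of observed imbalance, and this is a worse rule than a fixed prognostic list. Applied mechanically it makes the 95% limits slightly too wide: at most 2 to 3% at R² 10%, where it is close to simulation error, and about 3 to 7% at R² 30% (8% by the large-sample formula). It forgoes about 1 to 3 points of power at 3 kg, without threatening the stated 90%, and about 3 to 13 points if the true difference is 2 kg, which is smaller than the design assumes. These sizes rest on the assumed number of candidates, R² and thresholds, and on ignoring clustering by week.

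The documents do not show that the limits are too narrow, that false positives are inflated, or that the model will be chosen from the results.

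**What to change.** In section 3.3.1, delete the second half of the adjustment sentence, everything after the mention of recruitment center. Keep the baseline value and centre. Add a short named list of prognostic covariates recorded before allocation, and state that all of them are adjusted for whatever the observed balance. Age and booking BMI are natural examples, since section 3.1.5 already requires both for eligibility. Any model prompted by imbalance should be reported only as a labelled sensitivity analysis.

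The cost is one sentence, no new data collection for those two variables, and a few degrees of freedom out of about 200 evaluable women.

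### With about 40% loss planned, the main 12-month result is a complete-case ANCOVA that ignores the 6-month weight; the imputation analysis should be promoted or replaced by a mixed model

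*Protocol article*

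**What the plan says.** Section 3.1.7 (Sample size) allows for "a 40% drop out rate (including women diagnosed with overt diabetes on the basis of a fasting glucose sample postnatal") and expects that "a trial of 340 women should yield 200 evaluable subjects (100 in each of the intervention and control groups").

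Section 3.3.1 (Statistical analysis) compares the 12-month outcomes by analysis of covariance, adjusted for baseline, centre and chance imbalances, with standard errors corrected for randomisation by week. Multiple imputation by chained equations is named as a sensitivity analysis for key outcomes: "We will use this approach to impute 10 complete datasets and analyze them appropriately to provide results which take account of missingness". The section continues "For key outcome variables, this analysis will be reported in addition to the complete case analysis" and closes with "Analysis will be by intention to treat".

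Section 3.2.3.3 and Table 1 provide for weight at 6 and 12 months in both arms. Section 3.2.4.1 takes the 6-8 week postnatal weight as baseline.

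**The concern.** About 140 of the 340 randomised women (41%) are expected to be absent from the main estimate. A 12-month ANCOVA on complete cases also discards the 6-month weight of women who leave later, although that weight is likely to be the best available predictor of what is missing.

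The article gives reasons to expect dropout to follow early success, and to do so differently by arm:

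- The trial is unblinded, and only intervention women receive texts, monthly calls and the weight-management programme (sections 3.1.4, 3.2.1, 3.2.3.2).
- A second funded membership goes to those who attended well or lost weight (section 3.2.3.2), so continued contact is tied to early results.
- The programme audit in the Introduction reports a mean change of -4.0% overall and -5.5% in the 58.1% who attended most sessions. This implies about -(4.0 - 0.581 x 5.5)/0.419 = -1.9% in the rest. Low attendance is not trial dropout, but it points to less engaged women losing less.

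At stake is a spurious or inflated benefit in the estimate that the article ranks first.

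**Working it through.** **1. The plan's own figure.** The inputs from section 3.1.7 are "standard deviations of 7.0 and 3.9 kg in the intervention and control groups, respectively", 100 evaluable women per arm and a 3 kg difference. Section 3.1.2 gives equal allocation.

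- Evaluable women: 340 x 0.6 = 204, against 200 stated.
- SE of the difference = sqrt((7.0² + 3.9²)/100) = sqrt(0.642) = 0.801 kg.
- Power = Φ(3/0.801 - 1.96) = Φ(1.78) = 96%.

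The stated power above 90% is reproduced after the planned loss. The issue is bias, not power.

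**2. Bias of the complete-case estimate.** These assumptions are not in the documents: 40% loss in each arm; true effect zero; correlation 0.8 between 6- and 12-month weight change; and, in the intervention arm only, odds of later dropout rising by 1.35 or 1.65 per SD of worse 6-month change. Let e be the share of women lost early for unrelated reasons.

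- Later loss among those still in the trial: q = (0.40 - e)/(1 - e).
- Bias, to first order: b = ln(OR) x q x 0.8 x 7.0 kg.
- Type I error = Φ(-1.96 + b/0.801) + Φ(-1.96 - b/0.801).

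| Early, non-selective loss | q | OR 1.35 | OR 1.65 |
|---|---|---|---|
| 0 of 40 points | 0.400 | 0.67 kg, 13% | 1.12 kg, 29% |
| 20 of 40 points | 0.250 | 0.42 kg, 8% | 0.70 kg, 14% |
| 30 of 40 points | 0.143 | 0.24 kg, 6% | 0.40 kg, 8% |

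Simulation of 340 women under the same assumptions agrees. With no early loss it gives about 0.65 and 1.0 to 1.1 kg (13% and 27 to 28%). With 30 points early it gives about 0.23 and 0.4 kg (6% and 8%). The first-order formula runs slightly high at the larger odds ratio.

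**3. When there is no bias.** Let non-completers lose d kg less than completers, and let p be the fraction missing. The effect in all randomised women is then the complete-case effect - p_I d_I + p_C d_C. With p = 0.4 in both arms and a complete-case effect of 3 kg:

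- d = 3 kg in both arms: 3 - 1.2 + 1.2 = 3.0 kg.
- d = 3 kg in the intervention arm only: 3 - 1.2 = 1.8 kg.

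**4. What the 6-month weight adds.** A separate simulation assumed a true effect of 3.0 kg, correlation 0.7, a stronger dropout gradient (log-odds of 1 per SD, intervention arm only), and 6-month weight seen in all women.

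| Dropout depends on | Complete case | Imputation by arm, 10 datasets |
|---|---|---|
| nothing | 2.98 kg | 2.98 kg |
| 6-month change | 4.64 kg | 2.98 kg |
| unseen 12-month change | 5.36 kg | 4.28 kg |

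Using the 6-month weight removes the bias that it explains and reduces the rest. There is also a gain in precision. Under the assumptions of step 2, if half of the dropouts are weighed at 6 months, the SE is 0.736 against 0.808 kg, which is 9% smaller.

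**5. Ten imputations.** With a fraction of missing information f and m datasets:

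- Relative efficiency = 1/(1 + f/m). For f = 0.4 and m = 10 this is 96%.
- Rerun noise in the estimate = sqrt(f x 0.642/m): 0.16 kg at m = 10 and 0.08 kg at m = 40.
- Rerun variation of the SE = f/sqrt(2(m - 1)): 9.4% at m = 10 and 4.5% at m = 40.
- Datasets needed for 5% variation of the SE = 1 + 0.5(0.4/0.05)² = 33.

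In the simulation of step 4, f was only 0.27 to 0.32, because the 6-month weight carries information. Reruns of one dataset varied by 0.11 kg (SE by 8%) at m = 10 and by 0.06 kg (SE by 3%) at m = 40.

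**The case against.** The best defence is that the article already plans the remedy. Imputation is promised, the 6-month weight is collected, and nothing excludes it from the imputation model, whose variables an article may leave to the analysis plan. This stands: the bias figures show why such an analysis should come first, not that the planned check fails.

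The defence is also right that much of the 40% may not be selective on early weight change. It includes women excluded for overt diabetes around delivery or at 6 weeks, and section 3.1.4 foresees women who never attend after delivery. Before the 6-8 week visit the arms differ mainly by a one-hour session and a tracker. The split is not given, which is why the size is shown as a range.

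A reader might infer more than the documents support:

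- *That the sensitivity analysis is unstable.* Ten datasets are few for this much missing data, but about 96% efficient. Rerun noise matters only for a borderline result.
- *That the plan is defective for lacking an analysis under not-at-random dropout.* Missing at random is inferred from standard chained equations, and the article does not state it. A delta-adjusted analysis is detail that the fuller plan may hold.
- *That the intention-to-treat label is simply wrong.* Many use the term for analysis by allocated arm. The fair criticism is that the label sits beside a main estimate that leaves out four in ten women.

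**Conclusion.** The point holds as a matter of which analysis comes first. The article ranks the more bias-prone analysis above one that can use the 6-month weight, while planning to lose about 140 of 340 women.

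Under the stated assumptions the complete-case bias runs from about 0.2 to 0.4 kg (type I error 6 to 8%), if three quarters of the loss is early and non-selective, to 0.65 to 1.0 kg (13 to 27%), if all of it is selective. The odds ratios, the correlation, the restriction to the intervention arm and the early share are assumptions.

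It would go too far to say that the result will be biased, or biased in favour of the intervention. Complete-case ANCOVA is valid if dropout depends only on arm and the model's covariates. There is also no bias if the proportion lost and the resulting shift in kg are alike in both arms. Overstated benefit is the plausible direction, not a certain one.

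**What to change.** 1. In section 3.3.1, make the primary analysis one that includes all randomised women with any postnatal weight. It can be a mixed model using the 6- and 12-month weights, or multiple imputation by arm with the 6-month weight in the imputation model. Keep the adjustment for centre and the week-level correction of standard errors. In a mixed model, let the variances differ by arm, since the planning SDs are 7.0 and 3.9 kg.
2. Report the complete-case ANCOVA as supportive.
3. Raise the imputations from 10 to about 40.
4. Consider a delta-adjusted analysis, in which non-completers are assumed to do worse by stated amounts. This is a useful addition, not the correction of an error.

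The cost is a few sentences and slightly more programming, with no new data. The drawback is that the primary result then relies on the imputation or mixed-model assumptions. Women who leave before 6 months gain little from the change, and dropout that depends on unseen weight is only partly corrected.

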#### Focus groups

3.3.2

Women from the intervention group during their final visit will be invited to take part in focus groups (arranged for up to ten participants per group) to feedback on their experiences of the program and to suggest how the program might be improved. This feedback about will be their experience within the trial, including the research tools used, Slimming World referral, fitness tracker use, and the educational session will be important to inform any future trial design or future roll out of the intervention. Focus group sessions will be recorded using voice recorders with transcripts anonymized prior to analysis of feedback. Focus group participation will be optional and those women who take part will receive a multistore gift voucher to reimburse them for their time. All women in the intervention group will be asked to complete a questionnaire regarding feedback for the study.

## Discussion

4

The PAIGE2 study is a large-scale investigation into the implementation of an evidence-based pragmatic pregnancy and postpartum lifestyle intervention for overweight women with GDM. The study has been informed from the results of a pilot trial (PAIGE) (52), which provided promising results in postnatal weight reduction for mothers over a 6 month period. The study was developed taking account of the views of mothers with GDM, alongside a Project Steering Committee and patient group. The primary outcome of the PAIGE2 study is weight loss at 12 months postpartum.

A potential limitation of this study may be the differing nature of the healthcare systems in Northern Ireland and the Republic of Ireland. Obtaining ethical approval from the three Republic of Ireland hospital sites may prove difficult as the Republic of Ireland has no central ethics office/structure. However, the cross-border collaboration demonstrated in this trial should provide an evidence-based evaluation on the potential impact of a pregnancy and post-pregnancy lifestyle intervention for overweight mothers with GDM in an all-Ireland context. The cross-border approach should also identify optimum service delivery for successful implementation and impact of a lifestyle intervention for weight loss and GDM on the island of Ireland. Additional limitations may include participation-related factors, such as enrolment in Slimming World etc., which may influence their progress within the intervention. In addition, there may be some disparity between self-reported *vs* clinically measured body weight across the timepoints, and use of the fasting glucose immediately post-partum compared with 6 weeks postnatally to exclude diabetes. However, these will be minimized as much as possible by the research team.

The results from this study will be distributed to healthcare professionals through conference presentations and peer-reviewed journals to add to the current literature and evidence base for effective interventions to address this major public health issue.

